#### Outcomes {12}

The primary endpoint is the need for transfusion of at least one unit of PRBCs. This is a valid and easily available functional parameter mirroring the immediate clinical implications of blood loss and has direct relevance on patients’ health status.

Secondary endpoints are the number of transfused units per participant, the time between skin incision and beginning of transfusion, the estimated intraoperative blood loss, operation/anesthesia times, D-dimer levels before and after the operation, hemoglobin levels before and after the operation, duration of hospital stay, quality of life, and postoperative complications and mortality.

The number of transfused units per participant, estimated intraoperative blood loss, and time between skin incision and beginning of transfusion represent measures for assumed reduction and deceleration of bleeding. The operation and anesthesia times might be shorter with reduced bleeding. D-dimer levels are a pro-coagulation state measure and hemoglobin levels reflect the amount of blood loss. Duration of hospital stay, quality of life, and postoperative complications and mortality mirror the clinical impact of hemorrhage and transfusion.

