**Table Taba:** 

	**Study period**				
	**Screening**	**Enrolment and allocation**	**Post-allocation**		**Close-out**
**Timepoint**	*** − 14 to − 1 days***	**0**	***Operation***** + *****Intervention***	***1st post-operative day***	***Day of discharge, max. 30th post-operative day***

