**Assessments:**					
***Routine laboratory examination***^b^	X	(X)^a^		X	X
***Safety assessments (AE/SAE/AESI)***			X	X	X
***Transfusion Necessity***			X	X	X
***Concomitant medication***			X		
***Estimated intraoperative blood loss***			X		
***Operation***** + *****anesthesia duration***			X		
***Number of transfused PRBCs***			X	X	X
***Time to transfusion***			X	X	X
***Postoperative complications/mortality***			X	X	X
***Duration of stay***					X
***Quality of life (SF-12)***		X			X

^a^Pregnancy test: urine or blood beta-HCG within 72 h preoperatively in women of childbearing age

^b^Routine laboratory examinations: complete blood count, sodium, potassium, calcium, creatinine, and estimated GFR (MDRD formula), bilirubin, ALAT, ASAT, INR, apTT, D-Dimer levels

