### Data collection and management

#### Plans for assessment and collection of outcomes {18a}

All data of trial participants are assessed and collected by investigators and study nurses. Study visits take place upon recruitment (14 days to 1 day prior to surgery), on the day of surgery, on day 1 after surgery, and on the day of hospital discharge or postoperative day 30, whatever occurs first. Trial staff is specifically trained for data assessment and collection. Data on the primary endpoint, PRBC transfusion, is extracted from specific transfusion files and patient files or hospital information systems. Laboratory data is extracted from the laboratory systems of the trial sites. Validation certificates for the single laboratories need to be provided. Clinical data including intraoperative data are collected from patient files or hospital information systems. Quality of life is measured with the validated German version of the SF-12 questionnaire. The questionnaire is handed out to trial participants and collected by study staff after it has been filled by the participant. All collected data will be documented in the study-specific electronic case record form (eCRF) as promptly as possible. Any entry in the eCRF has to be traceable to the information contained in the source data. eCRF templates are available upon request from the principal investigator.

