### Statistical methods

#### Statistical methods for primary and secondary outcomes {20a}

The primary endpoint will be compared in the intention-to-treat population between the two study arms with a logistic regression model including the treatment group, and the stratification variables type of operation (esophagectomy, gastrectomy, colectomy, rectal resection, pancreatic resection, hepatectomy) and type of planned surgical access (open, minimally-invasive) as covariates.

The secondary endpoints of postoperative in-hospital complications and mortality will be analyzed similarly. The number of transfused units of PRBCs, estimated intraoperative blood loss, length of hospital stay, operation time, anesthesia time, D-dimer levels, and quality of life will be analyzed using a linear regression model including treatment group, type of operation, and type of surgical access as covariates. In case of heavy skewness in the outcome data, the outcome variables will be transformed to reduce skewness. All results for secondary outcomes will be interpreted in an exploratory sense. Dichotomous outcomes will be reported as absolute and relative frequencies and continuous variables by means, medians, standard deviations, and ranges. Time to transfusion will be compared between both arms using time-to-event analysis.

A safety analysis will be carried out by comparing the frequency of all adverse events and adverse events attributed to the intervention between the two study arms. Patients with a history of thromboembolic events will be analyzed as a subgroup of special interest.

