#### Methods in analysis to handle protocol non-adherence and any statistical methods to handle missing data {20c}

The primary analysis data set is the intention-to-treat population. This data set contains all patients who have been enrolled in the clinical trial and randomized. The secondary analysis data set is derived from the per-protocol population. This data set includes all patients who have been treated according to the protocol during the whole duration of the study and reached a defined endpoint. The tertiary analysis data set (safety population) contains all patients who have received at least one dose of study medication. There are no specific statistical methods stipulated to handle missing data, because the proportion of patients with missing endpoint data is expected to be very low.

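### Length of stay is observed only to postoperative day 30 and can end in death, but the linear regression fixed for it handles neither case (minor; exploratory endpoint)

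*Protocol article*

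**What the plan says.** All references are to the protocol article.

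- **Endpoint.** Outcomes {12} lists "duration of hospital stay, quality of life, and postoperative complications and mortality" among the secondary endpoints.
- **Collection.** In the schedule under Participant timeline {13}, the row "Duration of stay" has one mark, in the close-out column. That column is headed "Day of discharge, max. 30th post-operative day". Plans for assessment and collection of outcomes {18a} agrees: the last visit is "on the day of hospital discharge or postoperative day 30, whatever occurs first".
- **Model.** Statistical methods {20a} states that "length of hospital stay, operation time, anesthesia time, D-dimer levels, and quality of life will be analyzed using a linear regression model", adjusted for treatment group, type of operation and surgical access. The one adjustment offered is: "In case of heavy skewness in the outcome data, the outcome variables will be transformed to reduce skewness".
- **Population.** Section {20c} makes intention-to-treat the primary analysis set: "This data set contains all patients who have been enrolled in the clinical trial and randomized". In-hospital deaths therefore belong to it. The same section stipulates no method for missing data.
- **Methods used elsewhere.** Section {20a} also says: "Time to transfusion will be compared between both arms using time-to-event analysis". No such method is assigned to length of stay.

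**The concern.** Two groups of patients have no observed time of discharge under this schedule. For those still in hospital at day 30, it is known only that the stay exceeds 30 days. Those who die in hospital are never discharged. Linear regression needs one completed number per patient, and the article does not say what that number is for either group.

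If the days recorded at close-out are used as they stand, every stay beyond day 30 is shortened to 30, which pulls the arms together. An early death enters as a short stay, which favours the arm with more deaths. Leaving deaths out would instead condition on survival.

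The result has some weight for the reader. The Discussion expects that, with positive results, hospital stay would be shortened and costs saved by avoiding prolonged stays. A biased estimate of days saved would feed into that argument.

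**Working it through.** **What can be reproduced.** The article gives no figure for length of stay. Its only sample-size figure belongs to the primary endpoint and is not touched: 30% against 20%, two-sided 5%, 90% power gives 412 per group with continuity correction, and 412 / 0.97 = 424.7, so 425.

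**Assumptions for the illustration (none from the documents).** Stay S, counted from surgery, is log-normal with control median m of 10 to 14 days and log-SD σ of 0.6 to 0.7. TXA shortens every stay by 10%, so its median is 0.9m. Arms have 425 patients, as planned. Stays beyond day 30 are entered as 30.

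**Formulas.** With k = ln(30/m)/σ:
- share beyond day 30 = 1 − Φ(k)
- true mean = m·exp(σ²/2), so the true difference is 0.1 × this mean
- capped mean = m·exp(σ²/2)·Φ(k − σ) + 30·(1 − Φ(k))
- capped log mean = ln(m)·Φ(k) − σ·φ(k) + ln(30)·(1 − Φ(k))

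**Worked case, m = 12 and σ = 0.7.** k = ln(2.5)/0.7 = 1.309, so 9.5% of control stays exceed day 30. The true mean is 15.33 days and the true difference 1.53 days. The capped means are 14.03 (control) and 12.88 (TXA), a difference of 1.15 days. The loss is 1 − 1.15/1.53 = 25%. On the log scale the true difference is −ln(0.9) = 0.105 and the capped difference 0.097, a loss of 8%.

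| m, σ | Control stays > day 30 | Raw difference, true → capped (days) | Raw loss | Log difference, true → capped | Log loss |
|---|---|---|---|---|---|
| 10, 0.6 | 3.4% | 1.20 → 1.08 | 9% | 0.105 → 0.102 | 3% |
| 12, 0.6 | 6.3% | 1.44 → 1.21 | 16% | 0.105 → 0.100 | 5% |
| 12, 0.7 | 9.5% | 1.53 → 1.15 | 25% | 0.105 → 0.097 | 8% |
| 14, 0.7 | 13.8% | 1.79 → 1.21 | 32% | 0.105 → 0.092 | 12% |

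A wider range (σ from 0.5 to 0.9) puts 1.4% to 20% of control stays beyond day 30. The raw difference then goes from 1.13 to 1.09 days in the mildest case and from 2.10 to 1.05 in the worst.

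**Effect on the test.** Expected z = difference / √((variance₁ + variance₂)/425). In the order of the table:
- raw scale: 2.33 → 2.43, 2.33 → 2.46, 1.93 → 2.10, 1.93 → 2.11
- log scale: 2.56 → 2.55, 2.56 → 2.54, 2.19 → 2.17, 2.19 → 2.15

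The cap trims variance as well as the difference, so the ability to detect a difference hardly changes.

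**Deaths.** The Background shows that deaths must be expected: for gastrectomy and esophagectomy, hemorrhage in up to 5% with failure to rescue of up to 30% gives up to 0.05 × 0.30 = 1.5% from hemorrhage alone. If stay is otherwise equal, the spurious difference is (mortality difference) × (mean stay − mean day of death). Assume 2 percentage points, capped mean stay 11.67 to 15.79 days, and death on average on day 5 to 10:
- smallest: 0.02 × (11.67 − 10) = 0.03 day
- largest: 0.02 × (15.79 − 5) = 0.22 day

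The arm with more deaths looks shorter by that amount.

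**The case against.** The strongest reply is that the visit schedule fixes when the last visit occurs and does not define the variable. Section {18a} takes clinical data from patient files or hospital information systems, so a true discharge date might be retrieved. A condensed article may also leave the coding of unusual cases to the analysis plan. This stands in part. A reader might infer that the protocol enters 30 as the true stay and counts deaths as short stays, but no sentence says so. Both are what follows if the schedule and the model are applied as written. What remains is that the article does not leave the model open. It names one that cannot represent a censored stay or a stay without discharge, and an analysis plan that follows the article inherits this.

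A second reply is that skewed stay data would be transformed, so the raw-scale loss overstates the problem. This stands: on the log scale the loss is 3 to 12%, not 9 to 32%. The transformation reduces the attenuation but does not remove it, because a stay cut at 30 is still cut at 30 after taking logs.

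A reader might also infer that the cap hides the part of the distribution where a benefit would show. The figures do not support that: 68 to 91% of the raw difference remains, and the test statistic is essentially unchanged. The cap also creates no difference where stay is the same in both arms.

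Finally, a reader might extend the criticism to time to transfusion. The article names only time-to-event analysis there and fixes no censoring rule, so there is nothing to contradict.

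**Conclusion.** The point holds as a minor one. Collection stops at day 30, all randomized patients including deaths belong to the primary analysis set, and the stated linear model with an optional transformation deals with neither ongoing stays nor deaths. Applied to the recorded days, it would understate the difference in stay and slightly favour the arm with more deaths.

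The size rests entirely on assumed stay distributions, mortality and timing of death, because the documents give no distribution of stay. Under the main assumptions, the bias in the estimate ranges from small to about a third on the raw scale and is at most about an eighth on the log scale. The death effect is a fraction of a day. Mortality is analysed as its own secondary endpoint, so an imbalance would be visible beside the stay result. All secondary results are declared exploratory, and the confirmatory conclusion does not depend on this endpoint.

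**What to change.** Replace the linear model for length of stay with an analysis of time from surgery to discharge alive. Censor administratively at day 30 and treat in-hospital death as a competing event. Report cumulative incidence by arm, with a Fine-Gray or cause-specific model that uses the same covariates (treatment, type of operation, surgical access). This costs analysis wording only and needs no new data.

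If a difference in days is preferred, record the actual discharge date for patients still in hospital at day 30 and state explicitly how deaths enter the analysis. This costs one extra date for a minority of patients (about 14 to 59 of 425 controls under the assumptions above: 425 × 3.4% and 425 × 13.8%). The extra date alone does not settle the deaths, so the rule for them is needed as well. Neither option changes the sample size or the primary analysis.

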### Assignment of interventions: allocation

#### Sequence generation {16a}

Participants will be randomized within 24 h prior to surgery in a 1:1 ratio to the TXA or the placebo group. Randomization will be stratified by planned surgical access (open vs. minimally invasive) and planned operation (esophagectomy, gastrectomy, colectomy, rectal resection, pancreatic resection, or hepatectomy). Randomization will be done via an online tool (secuTrial®) generating a randomization number.

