#### Methods for additional analyses (e.g., subgroup analyses) {20b}

Subgroup analyses will be conducted according to surgical access (open vs. minimally-invasive), kind of operation (esophagectomy, gastrectomy, colectomy, rectal resection, pancreatic resection, or hepatectomy), and for patients with a history of a thromboembolic event.

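### The stated linear model for D-dimer and SF-12 leaves out the preoperative values the trial already collects, which gives up precision at no saving

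*Protocol article*

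**What the plan says.** **Measurement.** Outcomes {12} lists among the secondary endpoints "D-dimer levels before and after the operation, hemoglobin levels before and after the operation". In the Participant timeline {13}, the footnote to the routine laboratory row includes D-dimer ("bilirubin, ALAT, ASAT, INR, apTT, D-Dimer levels"). That row is marked at screening, on the first postoperative day and at close-out. The SF-12 row is marked at enrolment/allocation and at close-out. Each measure therefore has a scheduled preoperative value.

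**Analysis.** Statistical methods {20a} puts both under one linear model: "D-dimer levels, and quality of life will be analyzed" and then "using a linear regression model including treatment group, type of operation, and type of surgical access as covariates". Skewed outcomes are to be transformed, and all secondary results are to be read as exploratory. The section does not say whether the outcome is the postoperative value or the change.

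**Labels.** Sequence generation {16a} states: "Randomization will be stratified by planned surgical access (open vs. minimally invasive) and planned operation". The primary model in {20a} calls both factors stratification variables and attaches *planned* to access but not to operation. The linear model attaches it to neither. The subgroup section {20b} reads "Subgroup analyses will be conducted according to surgical access (open vs. minimally-invasive), kind of operation", again without it.

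**The concern.** The covariates are written out as a specific list, so on its face the article makes a choice here and is not merely silent. For a quantity measured before and after treatment, the patient's own starting value is usually among the strongest predictors of the later value. Without it, stable differences between patients stay in the residual, and a chance difference between arms at baseline is not removed from the estimate. Neither effect biases a randomized comparison. The result is a wider confidence interval than the collected data could give.

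What is at stake is the precision of two secondary results: D-dimer, which the article uses as a marker of a pro-coagulation state, and quality of life.

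**Working it through.** **The plan's own figure.** Sample size {14} gives 30% against 20%, two-sided 5%, power 90%, and 412 per group.

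- Without continuity correction: n = [1.960·√(2·0.25·0.75) + 1.282·√(0.30·0.70 + 0.20·0.80)]² / 0.10² = 392.
- With continuity correction: (n/4)·[1 + √(1 + 4/(n·0.10))]² = 412, the stated figure.
- With 3% non-compliance: 412/0.97 = 424.7, so 425.

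These figures concern transfusion only, and nothing below changes them. The 412 is used below only as a convenient number analysed per group.

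**Effect of the missing baseline.** Let ρ be the correlation between the preoperative and postoperative value within arm, after allowing for operation and access. The documents do not give it, so 0.3, 0.5 and 0.7 are assumptions. With the postoperative value as outcome:

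- Variance with baseline / variance without = 1 − ρ².
- Group size that the model without baseline would need for the same precision = 412/(1 − ρ²).
- Standardized difference detectable with 90% power, without baseline: (1.960 + 1.282)·√(2/412) = 0.226. With baseline: 0.226·√(1 − ρ²).
- Power with baseline for an effect that has 80% power without it: Φ[(1.960 + 0.842)/√(1 − ρ²) − 1.960].

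| ρ (assumed) | Variance factor | Equivalent n per group | Detectable difference at 90% power (SD) | Power instead of 80% |
|---|---|---|---|---|
| none (model as stated) | 1.00 | 412 | 0.226 | 80% |
| 0.3 | 0.91 | 453 | 0.215 | about 84% |
| 0.5 | 0.75 | 549 | 0.196 | about 90% |
| 0.7 | 0.51 | 808 | 0.161 | about 97.5% |

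**If the outcome were the change.** With equal variances before and after (a further assumption), the variance of a change relative to that of a postoperative value is 2(1 − ρ): 1.4, 1.0 and 0.6 at the same three correlations. The baseline-adjusted model gives 0.91, 0.75 and 0.51, so it is more precise under either reading of the outcome.

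**The labels.** Read together, {16a} defines planned access and planned operation, and the primary model in {20a} calls its two factors stratification variables. In that same sentence operation already lacks *planned*. Absence of the word therefore does not mark a switch to performed values.

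**The case against.** **Randomization already protects the estimate, and the endpoints are exploratory.** This is correct. The model without baseline is unbiased, its confidence interval already reflects chance imbalance, and {20a} claims nothing confirmatory for these endpoints. That limits the importance of the point. It does not remove the gain, which needs no new data.

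**A statistical analysis plan may add the baseline.** It may. The article nevertheless prints a specific covariate list, and that list is what a reader can assess.

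**A reader might infer a stronger point about access.** Since the linear model and the subgroups drop *planned*, one could conclude that performed access will be used. Performed access is settled after the bolus and could change with bleeding, so adjusting or subgrouping by it could bias the effect. The documents do not support that conclusion. No section says that performed access is used, none mentions conversion, and the primary model names planned access.

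Nor does a simple example establish bias in the D-dimer or SF-12 models. Take the planning risks of 30% and 20%, and assume conversion in 20% of patients with transfusion-level bleeding and 5% without. Among non-converted cases:

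- The risk difference is 0.24/0.905 − 0.16/0.92 = 0.091, against 0.100 overall.
- The odds ratio is (0.16/0.76)/(0.24/0.665) = 0.583, the same as overall: (0.20/0.80)/(0.30/0.70) = 0.583.

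The example concerns transfusion, which is analysed by logistic regression, and on that scale nothing moves. What stands is an inconsistent label.

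**A reader might also infer that hemoglobin has been left without an analysis**, since {20a} does not name it. A condensed article can leave that detail to the analysis plan, so it is not counted here.

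**Conclusion.** The point holds as a modest improvement. Preoperative D-dimer and SF-12 are scheduled, and the stated model does not use them. If the outcome is the postoperative value, adjustment would reduce the variance of the treatment effect by 9%, 25% or 49% at correlations of 0.3, 0.5 or 0.7. These correlations are assumed, and the real gain depends on values the documents do not give. No bias is shown, either from the missing baseline or from the access label. The primary analysis and the sample size are untouched.

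**What to change.** In Statistical methods {20a}, or in the analysis plan before unblinding:

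1. Analyse postoperative D-dimer and the SF-12 component scores by analysis of covariance: treatment group, planned operation, planned surgical access and the endpoint's own preoperative value. If the outcome is transformed for skewness, put the baseline on the same scale.
2. Name the postoperative time point used as outcome. For D-dimer the schedule offers two, the first postoperative day and close-out.
3. Hemoglobin, also measured before and after surgery, can be handled in the same way.
4. As a wording harmonization, write *planned operation* and *planned surgical access* in {20a} and {20b}, so that they match {16a}.

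The cost is a few words of analysis text. All the values are already scheduled, no visit or sample is added, and the number of patients does not change.

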#### Interim analyses {21b}

If deemed necessary after due consideration by all of its members, the data safety monitoring board (DSMB) may initiate an unplanned interim analysis regarding safety and efficacy at any time point during the trial. The DSMB will then give recommendations to the principal investigator for continuation, discontinuation, modification, or termination of the study.

The Sponsor, the authorities, and the competent ethics committee have the right to discontinue the trial prematurely in consequence of the results of the interim analyses if a new finding concerning significant superiority or inferiority in one of the treatment arms, with regard to the primary endpoint data, arises or if unacceptable risks and toxicities have occurred.

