### Trial design {8}

This trial has a multicenter, double-blind, placebo-controlled, 1:1 ratio parallel-group, randomized superiority design. It represents a low-intervention clinical trial according to Clinical Trials Regulation (EU) 536/2014.

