#### Sample size {14}

The sample size calculation is based on the assumption derived from the literature and own hospital data that in the control group (placebo), 30% of participants require intra- or postoperative transfusion of at least one unit of PRBCs [1, 29], and that the intervention (TXA) achieves a relative risk reduction of 33% [18], reducing the probability to 20%. This difference would not only be expected, but also represents a clinically meaningful value. With a type one error (alpha) of 5% and a power of 90%, using a two-sided *χ*^2^ test, this results in 412 participants per group (Software PASS).

Given that the primary endpoint is ascertained at the end of each participant’s hospital stay, virtually no loss to follow-up is expected. Non-compliance, i.e., withdrawal of consent during the study period, i.e., the hospital stay, is expected in 3% of patients, resulting in 425 participants per group to be randomized.

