#### Composition of the data monitoring committee, its role and reporting structure {21a}

An independent Data Safety Monitoring Board (DSMB) has been established to monitor safety data during the course of the clinical study. It comprises one expert each from surgery, anesthesiology, transfusion medicine, and biostatistics as well as a patient representative. The DSMB will receive regular information on safety events occurring in trial participants, in particular details on all reported SAEs, every 3 months during the trial period, and then convene for virtual meetings. This anonymized information will be prepared by the KKS. Moreover, if deemed necessary after due consideration by all of its members, the DSMB may initiate an unplanned interim analysis regarding safety and efficacy at any time point during the trial. The DSMB will give recommendations to the coordinating investigator for continuation, discontinuation, modification, or termination of the study.

All members of the DSMB are completely independent of the trial steering committee and investigators participating in the conduct of the trial. Their work is not subject to any directives by the aforementioned persons. In addition to its safety tasks, the DSMB provides the funding agency every 6 months with information about the trial progress and, if deemed necessary, provides advice regarding modifications of the original funding and time plan.

The composition and responsibilities of the DSMB and the structure and procedures of its meetings are laid down in a DSMB charter, which is available upon request from the principal investigator.

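### Unplanned efficacy looks may end the trial for significant superiority at an unstated level, so the 5% type I error is not guaranteed

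*Protocol article*

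**What the plan says.** Three parts of the protocol article bear on this.

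- **Interim analyses {21b}.** If its members judge it necessary, the DSMB "may initiate an unplanned interim analysis regarding safety and efficacy at any time point during the trial". It then makes recommendations to the principal investigator. A second paragraph gives the sponsor, the authorities and the ethics committee a right to end the trial early on the interim results, either for unacceptable risks and toxicities or "if a new finding concerning significant superiority or inferiority in one of the treatment arms, with regard to the primary endpoint data, arises".
- **Composition of the data monitoring committee {21a}.** The permission is repeated: "the DSMB may initiate an unplanned interim analysis regarding safety and efficacy at any time point during the trial". The regular three-monthly DSMB reviews are described separately, as reviews of safety events.
- **Sample size {14}.** "With a type one error (alpha) of 5% and a power of 90"% and a two-sided χ² test, "this results in 412 participants per group (Software PASS"). This is the only significance level in the article.

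The background section calls for a confirmatory trial. The statistical methods section compares the arms on the primary endpoint with one logistic regression and mentions no adjustment for earlier looks.

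**The concern.** A two-sided 5% test keeps its error rate when it is the only opportunity to declare superiority. Here the article opens further opportunities: efficacy may be examined at any time, the number of looks is not limited, and significant superiority on the primary endpoint is a named ground for ending the trial. Nothing in the text defines significance at such a look, and nothing lowers the level of the final test to pay for it.

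At stake is the error rate behind the trial's main claim. The discussion section says a positive result would support routine use of tranexamic acid in major abdominal surgery. If the trial stopped on an unadjusted interim result, that claim would not carry a 5% error rate. The estimated effect would also tend to be exaggerated, because stopping selects favourable fluctuations.

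**Working it through.** **1. Is any alpha held back for interim looks?** Reproduce the stated sample size.

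Inputs from Sample size {14}: in the control arm, "30% of participants require intra- or postoperative transfusion of at least one unit of PRBCs"; the intervention "achieves a relative risk reduction of 33% [18], reducing the probability to 20"%; two-sided alpha 0.05; power 0.90. From Trial design {8}: "1:1 ratio parallel-group, randomized superiority design".

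Pooled two-proportion formula, with mean rate 0.25 and difference d = 0.10:

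n = [1.960·√(2·0.25·0.75) + 1.2816·√(0.30·0.70 + 0.20·0.80)]² / 0.10²
= (1.2002 + 0.7795)² / 0.01 = 391.9, so 392.

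With continuity correction:

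n_c = (n/4)·[1 + √(1 + 4/(n·d))]² = (391.9/4)·[1 + √(1 + 4/39.19)]² = 411.7, so **412**, as stated.

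For 3% non-compliance: 412/0.97 = 424.7, so **425**, as stated.

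Both figures reproduce exactly with the full two-sided 5% spent on a single analysis. This is a fixed-sample design with nothing set aside for interim looks.

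**2. What does one unadjusted look do?** Assumptions: *significant* is read at 5%, the only level given; there is one interim look at information fraction t; and the final test stays at 5%. Under the null hypothesis the interim and final statistics Z₁ and Z₂ are standard normal with correlation √t, so

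overall error = 1 − P(|Z₁| < 1.96 and |Z₂| < 1.96).

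| Information at the look | Overall two-sided error |
|---|---|
| 25% | 9.1% |
| 50% | 8.3% |
| 75% | 7.3% |

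**3. More looks.** With equally spaced looks, each at 5%, two interims plus the final test give 10.7% and three plus the final give 12.6%. These show direction only; the article sets no schedule of efficacy looks.

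**4. What does a boundary restore, and at what cost?** One look at 50% information:

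- *Lan-DeMets O'Brien-Fleming-type spending.* Alpha spent at the look is 2·[2 − 2Φ(2.2414/√0.5)] = 0.0031, giving |Z| > 2.963. The final critical value that brings the total to 0.050 is 1.969 (nominal p = 0.0490).
- *Haybittle-Peto.* Interim p < 0.001 with the final test left at 0.05 gives 0.0502 overall.

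Power at 412 per group, 30% versus 20%, normal approximation with unpooled variance: expected Z = 0.10/√[(0.21 + 0.16)/412] = 3.337. The fixed design has power 91.6%. With the 2.963/1.969 boundary it is 91.5%, a loss of about 0.1 percentage point.

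**The case against.** The strongest reply is that nothing has gone wrong yet. No interim analysis is planned, a look needs due consideration by all DSMB members, and the right to stop is a discretionary power rather than a rule that compels action. The article condenses a fuller protocol and refers to a DSMB charter; a boundary could sit there or in the analysis plan, neither of which is shown. Much of this stands, and it rules out several stronger readings that a reader might draw.

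- *The 5% fails outright.* Not supported. If no efficacy look is taken, the single final test keeps its level.
- *The trial will stop at p < 0.05.* Not supported. The level for *significant* is undefined; reading it as 5% is an assumption, and a strict boundary would also fit the wording.
- *There will be an efficacy look at every DSMB meeting.* Not supported. The three-monthly meetings concern safety data, so they give no basis for counting five or more efficacy looks and quoting an error near 15%.
- *The sponsor will see comparative results.* This is an inference. The DSMB issues recommendations, and the sponsor's right to stop could operate through them. The wording is ambiguous on this.

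What the reply does not remove is that the article goes beyond leaving a detail to another document. It affirmatively permits efficacy looks at any time and names superiority on the primary endpoint as grounds for stopping, beside a fixed-sample 5% design. It points to no control elsewhere: it describes the charter as covering composition, responsibilities and meeting procedures.

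**Conclusion.** The concern holds in conditional form. The permission to look at efficacy and to stop for superiority is not reconciled with a design that spends its whole 5% on one final test, so the stated type I error is not guaranteed. It is 5% with no efficacy look. With one look at an unadjusted 5% it is about 7–9% (8.3% at half the information), and it rises with further looks. These sizes rest on assumptions about the level, number and timing of looks, none of which the article fixes; a strict boundary in an unseen document would remove most or all of the inflation. Because the issue touches the confirmatory claim and the correction is nearly free, it should be settled before any efficacy look is taken.

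**What to change.** **Preferred.** In sections {21b} and {21a}, limit unplanned interim analyses to safety, and delete superiority on the primary endpoint as a ground for stopping. The final test then keeps its full 5% and the sample size is unaffected.

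**Alternative, if early stopping for efficacy is wanted.** Prespecify the look or looks, with timing that does not depend on the observed effect, and state a strict boundary with the final critical value set to match. Examples for one look at 50% information are |Z| > 2.963 with 1.969 at the end (O'Brien-Fleming-type spending), or interim p < 0.001 with the final test at 5% (Haybittle-Peto, about 0.050 overall). A spending function added to the present wording would not be enough: it accommodates unscheduled looks only when their timing is unrelated to the accumulating effect, and here the DSMB may call a look whenever it sees a need.

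**In either case.** State that comparative interim results stay with the DSMB and that the sponsor receives only a recommendation.

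**Cost.** Wording in the protocol and the DSMB charter. The preferred option costs no power; the O'Brien-Fleming-type example costs about 0.1 percentage point at 412 per group. Neither needs extra patients.
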